## Abstract

**Background:**

Flexible fiberoptic bronchoscopy is being increasingly carried out under general anesthesia in pediatric patients. However, the optimal anesthetic protocol still remains unclear. This study aims to test the hypothesis that the addition of low-dose rocuronium during laryngeal mask airway-assisted flexible fiberoptic bronchoscopy in children can enhance procedural outcomes and improve overall management.

**Methods:**

In this randomized, double-blind, placebo-controlled trial, 140 children aged 1–6 years scheduled for flexible fiberoptic bronchoscopy under general anesthesia will be randomly allocated in a 1:1 ratio to either the rocuronium group or the normal saline group (*n* = 70 in each group). All children will receive intravenous propofol at a dose of 3 mg⋅kg^–1^ and remifentanil at 3 μg⋅kg^–1^ for anesthesia induction. This will be followed by either intravenous rocuronium at 0.3 mg⋅kg^–1^ or an equivalent volume of normal saline. Sevoflurane will be titrated to achieve the target anesthesia depth, while remifentanil will be initiated at a rate of 0.05 μg⋅kg^–1^⋅min^–1^ and subsequently adjusted as required. Mechanical ventilation will be performed via laryngeal mask airway and the bronchofiberscope is inserted through an adapter connected to the laryngeal mask airway. The primary endpoint, reflecting effectiveness of anesthesia, is the frequency of coughing episodes during the operation. Secondary endpoints include: (1) cumulative remifentanil dosage; (2) failure rate of flexible fiberoptic bronchoscopy operation; (3) hemodynamic changes; (4) cough scores in the post-anesthesia care unit; (5) procedure time; (6) discharge time; (7) adverse events; (8) satisfaction scores of bronchoscopist; (9) satisfaction scores of anesthesiologist; and (10) satisfaction scores of parents 24 h after the operation.

**Discussion:**

We hypothesize that the addition of low-dose rocuronium during laryngeal mask airway-assisted flexible fiberoptic bronchoscopy under general anesthesia may optimize operation conditions, reduce coughing frequency, lower remifentanil dosage and the failure rate, stabilize hemodynamic fluctuations, minimize adverse events and enhance satisfaction, thereby providing valuable reference for clinical anesthesia practice in these procedures.

**Study Protocol Registration:**

https://www.chictr.org.cn/showprojEN.html?proj=277486, identifier [ChiCTR2500105407].

## Introduction

Flexible fiberoptic bronchoscopy (FFB) maintains its critical role in pediatric pulmonology, serving indispensable diagnostic and therapeutic functions (1, 2). The guidelines of the British Thoracic Society (BTS) suggest that sedation should be recommended for all patients undergoing bronchoscopy unless there are absolute contraindications (3–5). Reducing coughing, providing a good operating environment without compromising airway patency, and maintaining adequate oxygenation are the primary goals of anesthesiologists.

The combined use of propofol and short-acting remifentanil is the most commonly used regimen during FFB (6, 7). The antitussive and analgesic properties of remifentanil may lead to a considerable reduction in coughing, thereby optimizing the working conditions for the bronchoscopist and improving patient comfort (1, 8–10). However, coughing reactions cannot be completely suppressed even when a high dosage of remifentanil is administered, and such a large dose of remifentanil is associated with more pronounced respiratory depression. The incidence of hypoxemia approaches 30% in children undergoing FFB while receiving remifentanil (1, 6, 11–14).

The technique of FFB via the laryngeal mask airway (LMA) was first introduced in 1989 and since then it has been described as a safe and convenient tool in both adult and pediatric populations (15–18). LMA with a bronchoscopy adaptor can direct the fiberscope to the glottis and provide ventilation without interfering with the maneuver of the bronchoscopist. Thus, this technology has the potential to overcome the side effects of hypoxemia during FFB, indicating that general anesthesia may be more preferable for FFB in children (15, 19–22). However, the decision of whether to use skeletal muscle relaxants remains a significant issue that anesthesiologists need to consider (23).

Several studies, as documented in case reports, have reported positive experiences with the use of neuromuscular blocking agents in LMA-assisted FFB (19, 23). However, there is currently no established guideline for the recommendation of neuromuscular blocking agents during anesthesia for FFB. Barclay et al.’s study demonstrated that the addition of low-dose rocuronium (0.3 mg⋅kg^–1^, equivalent to the Effective Dose 95) to propofol and alfentanil significantly improved the conditions for tracheal intubation after the induction of anesthesia (24). Gelberg et al.’s study showed that the addition of 0.2 mg⋅kg^–1^ of rocuronium to propofol and remifentanil during anesthesia induction in infants results in improved intubation conditions compared to placebo, although the difference did not achieve statistical significance (25). Both of the aforementioned studies imply that low-dose neuromuscular blocking agents may be beneficial for airway operations.

In this randomized placebo-controlled study, we hypothesize that the combination of propofol, remifentanil, and 0.3 mg⋅kg^–1^ rocuronium will optimize the examination conditions, effectively decrease the frequency of coughing, minimize the necessary dose of remifentanil, stabilize the hemodynamic fluctuations, and enhance the satisfaction of bronchoscopists, anesthesiologists, and patients. This approach aims to provide a valuable reference for clinical anesthesia practices during these procedures.

## Methods

### Study design

This single-center, double-blind, randomized, placebo-controlled trial will be conducted at Children’s Hospital of Soochow University, Suzhou, China. This trial protocol follows the guidelines of Standard Protocol Items: Recommendations for Interventional Trials (SPIRIT) (Supplementary File 1).

### Ethic approval and trial registration

The study protocol received approval from the Medical Ethics Committee of Children’s Hospital of Soochow University on May 30, 2025 (Approval No. 2025018, version 3.0) and was subsequently registered at the Chinese Clinical Trial Registry (Identifier: ChiCTR2500105407) on July 03, 2025. https://www.chictr.org.cn/showprojEN.html?proj=277486.

### Patients

An experienced anesthesia assistant will conduct a comprehensive screening of all the children to determine their eligibility and communicate with the parents or guardians of the children to encourage their active participation in the research. The principal and associate investigators will personally present the Participant Information and Consent Form in the guardian version, clearly delineating the study’s purpose, procedures, benefits, risks, and confidentiality policies. Additionally, they will provide the Participant Information and Consent Form in the children’s version, which is written in plain and age-appropriate language. They will also explicitly clarify the participants’ right to withdraw from the study at any time without incurring any adverse consequences. To be included in this study, children must meet the eligibility criteria, and their parents or guardians should provide written informed consent. A total of 140 eligible children scheduled for FFB under general anesthesia will be randomly assigned to either the rocuronium group or the placebo group, with 70 children in each group. The flow chart of this study is presented in Figure 1.

**FIGURE 1 F1:**
[figure not shown]
Flow chart of patients in this study. FFB, flexible fibreoptic bronchoscopy; LMA, laryngeal mask airway.

### Eligibility criteria

Inclusion criteria: (1) Aged between 1 and 6 years; (2) American Society of Anesthesiologists (ASA) physical status of II or III; (3) body mass index (BMI) between 14 and 18 kg/m^2^; (4) scheduled for FFB under general anesthesia due to conditions such as pneumonia, broncho-alveolar lavage (BAL), airway mucosal biopsy, or foreign body removal.

Exclusion criteria: (1) pulse oxygen saturation (SpO_2_) < 90% before FFB; (2) preoperative acute exacerbations of cough which is specifically defined as a clear increase in cough frequency to approximately twice that of the patient’s typical baseline pattern during the current illness, as reported by the parent/guardian, and this increase is not a feature of the child’s illness in the preceding days. This assessment will be guided by using a simple categorical scale: “Is your child coughing noticeably more often today than they were 2 days ago? Would you estimate it as “a little more,” “about twice as much,” or “much more than twice as much?”” A report consistent with “about twice as much” or “much more than twice as much” will meet this criterion; (3) history of allergy to relevant medications; (4) contraindications for the use of muscle relaxants such as mediastinal tumors; (5) hypertrophy of the tonsils and adenoids that may potentially affect the proper placement of the laryngeal mask; (6) second- or third-degree heart block; (7) history of asthma.

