### Study interventions

#### Anesthesia preparation stage

All children are screened for eligibility by an experienced anesthesia assistant who will not be involved in block sizes and future allocation. Baseline data including heart rate (HR), systolic blood pressure (SBP), diastolic blood pressure (DBP), pulse oxygen saturation (SpO_2_) are recorded. Children with a diagnosis of pneumonia or airway foreign body but with a stable, improving, or predictable pattern of cough will be eligible for inclusion. Their baseline cough frequency (“occasional” or “frequent but stable”) will be recorded as a characteristic for group comparison. Children are restricted from consuming solid foods for 6 h and clear fluids for 2 h prior to undergoing FFB (26). A patent intravenous cannula is inserted, and premedication with intravenous midazolam at a dose of 0.05 mg⋅kg^–1^ is given in the ward. Topical anesthesia is achieved by administering a 2-milliliter nebulized 2% lidocaine solution through inhalation before the procedure in the ward.

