### Secondary endpoints

The secondary endpoints are: (1) cumulative remifentanil dosage; (2) success rate of FFB operation; (3) hemodynamic variables; (4) cough scores in the PACU every 5 min; (5) procedure time defined as the duration from bronchoscope insertion to its removal; (6) discharge time which is defined as the interval from the removal of bronchoscopy until a modified Aldrete score of ≥9 is achieved; (7) adverse events that occur during the procedure and in the PACU, including desaturation (SpO_2_ < 90%) which is stratified into three categories: mild desaturation: 85% ≤ SpO2 < 90%, moderate desaturation: 80% ≤ SpO2 < 85%, severe desaturation: SpO2 < 80%; laryngospasma; sore throat; bradycardia or hypotension defined as a decrease of at least 20% below the age-adjusted lower limit of heart rate or arterial blood pressure; tachycardia or hypertension defined as an increase of at least 20% above the age-adjusted upper limit of heart rate or arterial blood pressure; (8) satisfaction scores of bronchoscopists during the operation; (9) satisfaction scores of anesthesiologists; (10) satisfaction scores of parents 24 h after the operation. Given the age range of our study population (1–6 years), this score is reported as a proxy measure by the child’s parent or guardian, who is present throughout the preoperative, recovery, and immediate post-discharge periods. Satisfaction scores are measured subjectively by a simple numeric score between 1 (highly dissatisfied) and 10 (highly satisfied).

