### Data collection and management

Demographic data include sex, age, weight, height, and BMI. Baseline characteristics encompass ASA physical status, as well as baseline values for HR, NIBP, SpO_2_, and baseline cough frequency (“occasional” or “frequent but stable”). Periprocedural data include the following: the total number of coughing episodes during the FFB intervention period; procedure time; cumulative remifentanil dosage; success rate of the FFB operation; HR, NIBP, SpO_2_, PetCO_2_, body temperature, BIS value, severity grading of pneumonia; the usage and dosage of sugammadex, the corresponding TOF ratio at the time of reversal; cough scores recorded in the PACU; discharge time; and adverse events that occurs during the procedure and in the PACU, including desaturation (SpO_2_ < 90%), laryngospasm, sore throat, bradycardia or hypotension, tachycardia or hypertension. Additionally, the data will capture anesthesiologist satisfaction, bronchoscopist satisfaction and parent satisfaction. All raw data will be meticulously documented in the Case Report Forms (CRFs) by an independent investigator. Upon completion of the trial for all patients, the principal investigator and the data administrator will jointly verify the integrity and accuracy of the data. Subsequently, the data administrator will import the verified data into a designated electronic database and forward it to a statistician for final statistical analysis.

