#### Statistical analysis

All data will be checked for normal distribution using the Kolmogorov test. For normally distributed data, continuous variables will be presented as mean ± SD and analyzed using the independent Student’s *t*-test. Nonnormally distributed data will be presented as the median and interquartile range (IQR) and compared using the Mann-Whitney U test where appropriate. Categorical data are presented as numbers (proportions, %) and will be analyzed using Fisher’s exact test or the chi-square test. For the study endpoints, 95% confidence intervals will be reported as appropriate to provide a more comprehensive understanding of the results.

The primary endpoint is the frequency of coughing episodes during the FFB operation period. If the primary endpoint adheres to a Poisson distribution or a negative binomial distribution, negative binomial regression is further utilized, adjusting for the influence of covariates [the severity classification of pneumonia, BMI, age, sex and operation time, baseline cough frequency (“occasional” or “frequent but stable”)]. If the primary endpoint conforms to a normal distribution, a multiple linear regression model is further adopted for the same covariate adjustment. Subgroup analyses for the primary endpoint will be performed according to age (<3 years old vs. ≥3 years old), sex (female vs. male), BMI (<15 vs. ≥15), operation type (BAL vs. BAL + airway mucosal biopsy vs. foreign body removal) and operation time (<20 min vs. ≥20 min). Recognizing the possibility of intra-observer variability in applying the cough threshold, we conducted a pre-specified sensitivity analysis for the primary endpoint. The frequency of coughing episodes will be re-calculated using two alternative, stricter definitions: “Worst-case” consolidation and “Best-case” granularity. The conclusions of the primary analysis are considered robust only if the between-group difference (rocuronium vs. normal saline) remained statistically significant (*p* < 0.05) in the same direction under both alternative sensitivity analysis scenarios.

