The secondary endpoints will be analyzed using the multivariate logistic regression model or the generalized linear model, adjusting for the same covariates as those of the primary endpoint. Repeated measurement data will be analyzed using a mixed linear model to compare haemodynamic variables and cough scores in the PACU between groups. To address the issue of multiple comparisons for adverse events observed in secondary endpoints, the Benjamini-Hochberg procedure will be employed to control the false discovery rate.

The analysis will be performed on the modified intention-to-treat population. To ensure robustness, a per-protocol analysis will additionally be conducted; however, the intention-to-treat approach will remain the primary basis for analysis. Missing data will be processed by multiple imputation and maximum likelihood method. All endpoints are performed at the two-sided 5% significance level. Statistical analyses will be performed using SPSS statistics (version 19.0; IBM SPSS, Chicago, IL, USA).

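### The desaturation model omits baseline SpO2, which is recorded and lies on the event's own scale; adding it is a small, nearly free gain, not the correction of an error

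*Protocol article*

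**What the plan says.** Four statements in the Protocol article bear on this point.

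- **Entry.** Eligibility criteria excludes children with "pulse oxygen saturation (SpO_2_) < 90% before FFB", so a child at exactly 90% may enter.
- **Event.** Secondary endpoints, item 7 (adverse events during the procedure and in the PACU), includes "desaturation (SpO_2_ < 90%) which is stratified into three categories". The grades are mild from 85% to below 90%, moderate from 80% to below 85%, and severe below 80%.
- **Baseline data.** Anesthesia preparation stage states: "Baseline data including heart rate (HR), systolic blood pressure (SBP), diastolic blood pressure (DBP), pulse oxygen saturation (SpO_2_) are recorded". Data collection and management again lists "baseline values for HR, NIBP, SpO_2_, and baseline cough frequency".
- **Analysis.** Statistical analysis names the primary endpoint's covariates as "the severity classification of pneumonia, BMI, age, sex and operation time, baseline cough frequency". The secondary endpoints then use a logistic or generalized linear model, "adjusting for the same covariates as those of the primary endpoint". For adverse events, "the Benjamini-Hochberg procedure will be employed to control the false discovery rate".

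Baseline SpO2 is therefore collected but is not in the adjustment set for desaturation.

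**The concern.** The covariate set was chosen for cough and carried over to every secondary endpoint. For desaturation it leaves out the one baseline value measured on the same scale as the event. If the lowest SpO2 follows the starting value, a child who enters at 90% has an event after a fall of about one point, while a child who enters at 99% needs a fall of about ten. Part of the variation in who has an event would then come from the starting value, and the model would leave it unexplained.

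The article reasons the other way for cough. Its limitations paragraph treats background cough propensity as a potential confounder, records baseline cough frequency and makes it a covariate. The haemodynamic adverse events are judged against age-adjusted limits, and age is in the model. Desaturation has a fixed line and no matching covariate.

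At stake are some power, and protection against a chance imbalance, in one safety comparison. That comparison has some weight: the Introduction puts hypoxemia near 30% in children given remifentanil during bronchoscopy and presents the laryngeal mask as a way to overcome it.

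**Working it through.** **The plan's own figure.** There is none to reproduce. The stated sample size concerns cough frequency, and the article gives no expected desaturation rate, no SpO2 distribution and no association between baseline and event. Every SpO2 input below is an assumption, except that the 30% control rate borrows the hypoxemia figure in the Introduction.

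**1. How far risk could depend on the starting value.** Assume an exponential fall with mean 4 points in controls. A child whose fall starts at level s has event risk exp(−(s − 90)/4).

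- Full tracking (s equals baseline): at 92, exp(−2/4) = 61%; at 96, exp(−6/4) = 22%; at 98, exp(−8/4) = 14%.
- Half tracking (s moves half as far from 96 as baseline does): at 92, s = 94 and exp(−4/4) = 37%; at 96, 22%; at 98, s = 97 and exp(−7/4) = 17%.

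**2. Power with and without baseline SpO2, first set of assumptions.** Baseline mean 96, SD 2.5, truncated at 90; fall halved by rocuronium; 66 children per arm; 1,500 simulated trials per scenario; likelihood-ratio test of treatment in a logistic model.

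| Tracking | Without | With | Gain (points) |
|---|---|---|---|
| 1.0 | 0.746 | 0.808 | 6.2 |
| 0.5 | 0.857 | 0.865 | 0.8 |
| 0.25 | 0.875 | 0.881 | 0.6 |

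The Monte Carlo standard error of one such power is about √(0.86 × 0.14/1500) = 0.009. The last two gains are therefore close to nothing.

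**3. Power, second set of assumptions.** Desaturation 30% vs 15%; 70 per arm; baseline SpO2 equal to 100 minus a gamma variable (shape 2, scale 1.5), truncated at 90; 4,000 trials per scenario.

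| Odds ratio per point lower SpO2 | Type I error, without / with | Power, without / with |
|---|---|---|
| 1.00 | 0.044 / 0.044 | 0.556 / 0.556 |
| 1.22 | 0.052 / 0.054 | 0.549 / 0.572 |
| 1.49 | 0.052 / 0.053 | 0.556 / 0.608 |

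Under no effect, the mean between-arm difference without adjustment was 0.0014, −0.001 and 0.0001 in the three rows. The gain is 0, 2.3 and 5.2 points, and there is no bias to remove.

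**4. Chance imbalance.** In the second simulation, the between-arm difference in mean baseline SpO2 had mean about 0 and SD about 0.33 points. A 2-SD imbalance is 0.66 points. At the strongest assumed association it would shift the desaturation odds ratio by a factor of about exp(0.66 × ln 1.49) = 1.3. A difference that large is uncommon, and the test's error rate already allows for it. Adjustment would remove most of its effect in the trial where it occurred.

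**5. Events per parameter.** At 30% vs 15% with 70 per arm, expected events are 70 × 0.30 + 70 × 0.15 = 31.5. The planned model has at least seven parameters besides the intercept (treatment and six covariates), or 31.5/7 = 4.5 events each. With baseline SpO2 this becomes 31.5/8 = 3.9.

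**The case against.** A reader might infer something stronger: that sharing the 90% line makes the endpoint defective, because it partly measures how close each child was to 90% at entry and so distorts the treatment comparison. The documents do not support that. Randomization and blinding specifies 1:1 random allocation, so closeness to 90% is balanced in expectation, and the simulation shows neither inflated type I error nor a shifted null difference. An absolute, graded threshold is a legitimate safety definition. Setting the entry floor at the same value means that no child meets the event definition at entry.

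Other objections reduce the size of the point, and these stand:

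- **Oxygen.** Under Anesthesia induction stage, children receive 100% oxygen by mask and then 50% through the laryngeal mask. The baseline is taken earlier, so an intraprocedural fall need not start from it. This undercuts the full-tracking scenario, which gave the largest gain. It bears less clearly on the PACU, where events also count and the article states no oxygen fraction.
- **Assumed inputs.** Halving the fall cuts the event risk at baseline 96 from 22% to exp(−6/2) = 5%, a large effect with no support in the documents.
- **Wrong comparator.** Both simulations compared treatment alone with treatment plus baseline SpO2. The planned model already contains pneumonia severity and age, which may carry some of the same information, though less so for foreign-body cases. The gain over the actual plan has not been shown.
- **Weight of the endpoint.** Desaturation is one of several adverse events within one secondary endpoint, under false-discovery-rate control. The article nowhere calls it the main safety outcome.

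None of this shows that prespecified adjustment does harm. Nor is the matter simply left to an unseen analysis plan, because the article itself fixes the covariate set for the secondary endpoints.

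**Conclusion.** The point holds as a minor, optional improvement. The plan carries a covariate set chosen for cough over to desaturation and omits a recorded baseline value on the event's own scale. This is not an error or a contradiction; it causes no bias, and the 90% definition can stay.

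The cost is about 0 to 6 points of power, with exposure to chance imbalance in one secondary safety item. That range rests on assumed SpO2 distributions, tracking and treatment effects, and on models without the six planned covariates. It would shrink if supplemental oxygen weakens the link to baseline. How many children will enter near 90% cannot be determined from the article.

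**What to change.** In Statistical analysis, where the secondary-endpoint models are described, add one sentence: the desaturation model includes baseline SpO2 as a continuous covariate. Fix the covariate set in advance. A rule that switches to a smaller set if events turn out few would add analytic flexibility without a defined trigger.

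Optionally, describe by arm the fall from baseline to the lowest recorded SpO2. SpO2 is monitored continuously during the procedure and every 5 min in the PACU, but the lowest value is not itself a listed data item, so the case report form should capture it if this is wanted.

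The cost is one sentence and no new baseline data. The covariates for this endpoint would differ from those of the other secondary endpoints, and the model would carry one more parameter, which matters somewhat if events are few.
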